### Intervention development

Initial development of the Trial Library intervention and subsequent development of this study protocol are the result of a collaborative effort of researchers, product and service design specialists, engineers, and consumers. Input from patients with prostate cancer during the design process, via patient interviews, has been instrumental in understanding how to create a tool that is accessible and informative. The primary end consumers of the Trial Library intervention are patients and caregivers. The goal of the development of this protocol is to propose methodology for developing and piloting technological interventions for equitable recruitment into clinical trials based on patient-centered design models while also considering clinical, sociological, and technological perspectives.

Information about clinical trials provided in this resource is intended to be useful, relevant, and accessible to all prostate cancer patients, while also aiming to address the informational needs of vulnerable and underrepresented patients. These aims were addressed in the product development process applying human-centered design methods and tools. Human-centered design incorporates the human perspective across a structured process to solve problems. In developing the Trial Library intervention, researchers first conducted a focus group of Black men with prostate cancer to gather information about what was considered to be relevant and desirable in a resource, and what beliefs and knowledge gaps existed about clinical trials that should be addressed in the design. Focus group findings were translated into the product features. User testing was then performed in clinic waiting rooms. A total of 35 men with prostate cancer, 66% of whom self-identified as Black, provided input in the development of the Trial Library intervention. Interviewees were shown select portions of Trial Library intervention and were asked a series of open-ended questions designed to capture patient understanding of clinical trials and to assess the clarity of the clinical trial matching questions. The feedback gathered from these interviews was used to refine the product in preparation for this study. In this study, the human perspective was gathered through interviews conducted with Black men with prostate cancer, and the information gathered from those interviews informed the specific design goals and content parameters of the Trial Library intervention. Table 3 illustrates themes identified from the focus group analysis.

**Table 3 Tab3:** User testing design principles

Design principles	Outputs
Design for flexibility and accessibility	Provide all website features at surface level (educational articles, matching tool, misc. resources) Universal navigation menu Contact info to Nurse Navigator for additional help
Be transparent and honest	Content is written in clear, concise plain language Provide disclaimer(s) re: accuracy of presented info
Having a “trustworthy” voice is better than a “legitimate” one	Content covers information that fits contextually to patients’ lifestyle and beliefs User testimonies
Facilitate a “safe space”	Conversational, empathetic tone Provide clear directions on how to access matching tool, but not in a forceful manner

### Methods

This is a mixed methods study design and will include quantitative surveys and qualitative interviews to assess the participant and physician experience with the Trial Library intervention. This study will also measure preliminary estimates of efficacy of the Trial Library intervention in promoting patient-physician discussion of clinical trials. Efficacy will be determined by whether a clinical trial discussion was documented in the electronic medical record during the clinic visit. All procedures have been approved by the UCSF Institutional Review Board for research on human subjects.

### Measures and statistical analysis

Patients will complete a self-administered survey on paper at the end of the clinic visit with multiple-choice questions (Additional file 1). The survey will include brief demographic questions about the patient’s education level and health literacy. Demographic characteristics will be collected from electronic medical record, including date of birth, race/ethnicity, preferred language, and zip code. Additionally, demographic characteristics of participants in the study will be compared to the overall demographic characteristics of patients with prostate cancer seen at HDFCCC to assess representativeness of the sample. Demographic and clinical characteristics will be summarized by descriptive statistics.

### Quantitative survey

The primary objective of this study is acceptability which will be a measure of overall satisfaction rate. Patients will respond to a set of multiple-choice questions on paper at the end of the clinic visit (Additional file 1). The survey will include a question about participant satisfaction with the study intervention and how the use of this intervention impacted their visit with their provider. In order to minimize human transcription error when inputting data from paper to a computer database, the study will use double entry verification.

### Sample size and justification

The sample size for this study is 66 participants. In the literature, 35% of patients with cancer utilize the Internet as a preferred source of health information over their provider [39]. To our knowledge, there is no data available on satisfaction rate with online health information; therefore, we use 35% as a proxy for satisfaction rate with online health information in this patient population. To measure the overall satisfaction rate of study participants, we will determine the proportion of participants who report some degree of satisfaction on a 5-item Likert scale from extremely dissatisfied to extremely satisfied with the Trial Library intervention by point estimation and its 95% confidence interval and will be compared to a proxy reference satisfaction rate of 35% by one-sample proportion test. In this pilot feasibility study, the null hypothesis that the true satisfaction rate (acceptability) is 35% will be tested against a one-sided alternative. The null hypothesis will be rejected if 29 or more satisfactions are observed in 66 participants. This design yields a type I error rate of 0.0487 and power of 0.8010 when the true satisfaction rate is 50%.

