## Discussion

This novel study leverages health information technology to develop an online informational resource for a diverse patient population. The principles that informed the design of the Trial Library intervention aim to be generalizable to clinical trials across many disease contexts. From the ground up, this resource is built to be inclusive of the linguistic, literacy, and technological needs of underrepresented patient populations.

This study will measure the acceptability of the Trial Library intervention among patients with prostate cancer seen at one academic medical center. The qualitative component of this mixed methods study will capture the participant and physician experience with the intervention. This study will provide critical preliminary data prior to a larger multi-site randomized clinical trial of the intervention. Positive results from this study would support the use of Internet-based recruitment tools as a viable method for recruiting diverse patient populations into clinical trials within a clinical setting. Additionally, preliminary data from this study may inform larger interventions delivering online health information to improve clinical trial recruitment in the community.

This study will also examine the physician perspective after incorporating a patient online trial resource in the clinical context. Given that this intervention is being tested in a closed system, the clinic, we will be able to assess the impact of the intervention on the patient and physician clinical experience. It is possible implementation of this study intervention may disrupt workflow and increase clinic length. This study is targeting new patients and measuring clinic visit time to capture these effects.

We anticipate limitations in this single site pilot study and will only capture preliminary estimates of efficacy. The intervention will only populate one clinical site’s available trials and be available in English. Future studies will include a translated copy of the website in Spanish and incorporate trial options for multiple clinical sites.

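### Rejecting the 35% null would not show that the tool is acceptable, because 35% is a rate of source preference and not a satisfaction floor

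*Protocol article*

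**What the plan says.** Under Quantitative survey, the protocol article sets the primary endpoint: "The primary objective of this study is acceptability which will be a measure of overall satisfaction rate".

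Sample size and justification gives the rest:

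- **Measure.** It is "the proportion of participants who report some degree of satisfaction on a 5-item Likert scale from extremely dissatisfied to extremely satisfied", reported as a point estimate with a 95% confidence interval.
- **Source of the reference rate.** The cited literature finds that "35% of patients with cancer utilize the Internet as a preferred source of health information over their provider".
- **Reason for borrowing it.** The authors know of no figure for the endpoint itself: "there is no data available on satisfaction rate with online health information".
- **How it is used.** The preference figure then stands in for the missing one: "therefore, we use 35% as a proxy for satisfaction rate with online health information in this patient population".
- **Test.** A one-sample proportion test, in which "the null hypothesis that the true satisfaction rate (acceptability) is 35% will be tested against a one-sided alternative".
- **Size and rule.** "The sample size for this study is 66 participants", and the null is rejected at 29 or more satisfied. The stated type I error is 0.0487, and the stated power is 0.8010 at a true rate of 50%.

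The article names no other minimum level of satisfaction.

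**The concern.** The reference rate and the endpoint measure different things. The 35% is a comparative choice between two information sources. The endpoint is a rating of one particular tool. A patient who prefers to hear from the provider may still be satisfied with the website, and the reverse is also possible. Exceeding 35% therefore has no direct meaning on the satisfaction scale.

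This matters because the null hypothesis equates the tested rate with acceptability, which is the primary objective. Whatever the test rejects becomes the study's primary conclusion. With a reference this low, the study could report a positive primary result although fewer than half of its participants said they were satisfied.

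**Working it through.** **Inputs** (all from Sample size and justification): n = 66, null rate p0 = 0.35 (one-sided), reject at r = 29 or more, design alternative p1 = 0.50.

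**1. The plan's own figures.** The chance of success at a true rate p is the exact binomial tail P(X ≥ r | n = 66, p).

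| Cutoff r | r/66 | p = 0.35 (type I error) | p = 0.40 | p = 0.45 | p = 0.50 (power) |
|---|---|---|---|---|---|
| 29 | 43.9% | 0.0832 | 0.297 | 0.615 | 0.866 |
| 30 | 45.5% | 0.0511 | 0.217 | 0.518 | 0.805 |
| 31 | 47.0% | 0.0298 | 0.152 | 0.420 | 0.731 |

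The stated 0.0487 and 0.8010 do not belong to a cutoff of 29. They lie closest to a cutoff of 30, but the exact calculation there does not give 0.0487 either. This is a separate error. It matters here only because the present point must not depend on it.

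**2. What the stated rule allows.** 29/66 = 43.9%, which leaves 66 − 29 = 37 participants, 37/66 = 56.1%, who are neutral or dissatisfied. Every count from 29 to 32 (32/66 = 48.5%) is a success with fewer than half satisfied.

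**3. Does correcting the cutoff remove the problem?** No. The lowest cutoff with exact type I error of at most 0.05 against 35% is 31, since 30 gives 0.0511. 31/66 = 47.0% is still below half, with 35 of 66 not satisfied. The low bar comes from the 35% itself.

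**4. How much comes from each source.** If true satisfaction were 40%, the rule would succeed with probability 0.297 at a cutoff of 29 and 0.152 at a cutoff of 31. About half of that success probability belongs to the cutoff error and the rest to the choice of 35%.

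**5. What the planned interval would show.** The exact two-sided 95% (Clopper–Pearson) interval at 29/66 is 31.7% to 56.7%. It displays the low rate plainly, and it also contains 35%.

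**6. Illustration of a floor on the satisfaction scale.** The 50% floor and the true rates below are assumptions; the article gives none. With 66 participants, require the one-sided 95% exact lower bound to exceed 0.50:

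- 40/66: lower bound 0.497, not enough.
- 41/66 (62.1%): lower bound 0.513, enough.
- Type I error of the rule of 41 or more: P(X ≥ 41 | 0.50) = 0.032.
- Power: 0.41 at a true 60%, 0.73 at 65%, 0.93 at 70%.

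**The case against.** The strongest reply is that the protocol hides nothing. It calls the study a pilot, says that no satisfaction data are known, labels 35% a proxy, and already plans a point estimate and interval. Acceptability is also explored in patient and physician interviews (Table 2). This makes the point one about the choice of benchmark, not about a contradiction. It also means that much of the remedy is already in the plan. It does not give 35% a meaning as a floor, and the interviews do not alter the prespecified rule.

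A second fair objection is that any replacement floor is a judgement. That stands. A 50% floor has a real cost: at a true rate of 60% it would pass only 41% of the time.

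Some stronger readings are tempting, but the article does not support them:

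- **Indifferent ticking would already beat the null.** A reader might argue that two of five categories count as satisfied, so random answers give 40%. The response wording is in an additional file not shown here, and nothing supports uniform ticking.
- **A weak result would trigger the randomized trial.** The article says that the pilot supplies preliminary data before that trial. It does not make the trial conditional on this test.
- **The Discussion draws its recruitment claim from satisfaction alone.** It says "Positive results from this study would support the use of Internet-based recruitment tools as a viable method for recruiting diverse patient populations". That sentence covers all study results, which include documented trial discussions and recruitment at about 30 days. The same section states the single-site and English-only limits.
- **Most participants could be dissatisfied.** The 56.1% includes neutral answers.

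**Conclusion.** The point holds as a weakness of the benchmark. The 35% measures which source patients prefer, so rejecting it does not establish that the Trial Library is acceptable. Success is possible at 43.9% satisfied under the stated rule, and at 47.0% under the lowest cutoff that holds 5%.

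These figures are exact binomial results from the protocol's own n, null and cutoff. They assume that all 66 participants answer the item and that every answer short of some satisfaction counts as not satisfied. The conclusion does not rest on 50% being the right floor, nor on the mismatch between the cutoff of 29 and its stated error rates, which needs its own correction.

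**What to change.** In Sample size and justification, and wherever acceptability is concluded:

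1. State that rejection of 35% will not be taken as evidence of acceptability. Make the primary result the satisfied proportion with its planned 95% confidence interval, and add the counts in all five response categories.
2. If a pass/fail rule is wanted, prespecify a minimum acceptable satisfaction rate on the satisfaction scale itself, give the reason for it, and derive the cutoff and power exactly. The 41-of-66 rule shown above for an assumed 50% floor is an illustration of the form, not a recommended value.

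Both options are changes of wording and analysis, with the same 66 participants and the same survey. The first gives up a formal success test. The second sets a harder criterion, with limited power if true satisfaction is only modestly above the chosen floor.

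### The primary rule of 29 or more satisfied out of 66 has an exact type I error of 0.083 and power of 0.866, not the stated 0.0487 and 0.8010

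*Protocol article*

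**What the plan says.** Everything needed is in the protocol article, section *Sample size and justification*.

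- Size: "The sample size for this study is 66 participants".
- Hypothesis: "the null hypothesis that the true satisfaction rate (acceptability) is 35% will be tested against a one-sided alternative".
- Rule: "The null hypothesis will be rejected if 29 or more satisfactions are observed in 66 participants".
- Claimed properties: "This design yields a type I error rate of 0.0487 and power of 0.8010 when the true satisfaction rate is 50" per cent.
- Analysis: the satisfaction rate is reported "by point estimation and its 95% confidence interval and will be compared to a proxy reference satisfaction rate of 35% by one-sample proportion test".

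No interim look or second stage is described. The section *Quantitative survey* makes acceptability, measured as overall satisfaction, the primary objective, so this is the decision rule for the primary objective.

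**The concern.** The section fixes the sample size, null rate, direction, cut-off and alternative rate. Type I error and power then follow by calculation, and nothing is left for a fuller document to settle. The printed error and power do not belong to the printed rule.

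A reader who relies on error control just under 5% is in fact given about 8.3%. At the boundary count, the rule and the named test also lead to different conclusions. The article presents the pilot as the source of preliminary data for a multi-site randomized trial, so a declaration of acceptability should carry the error rate attached to it.

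**Working it through.** **Inputs** (all from *Sample size and justification*): n = 66, p0 = 0.35, one-sided, reject if X ≥ 29, p1 = 0.50. Stated: error 0.0487, power 0.8010.

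**Step 1: try to reproduce the stated pair.** For a single-stage rule that rejects when X ≥ r:

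- type I error = P(X ≥ r), with X ~ Binomial(66, 0.35)
- power = P(X ≥ r), with X ~ Binomial(66, 0.50)

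| Reject if X is at least | Exact type I error | Exact power at 50% |
|---|---|---|
| 28 | 0.1287 | 0.9124 |
| **29 (printed rule)** | **0.0832** | **0.8661** |
| 30 | 0.0511 | 0.8055 |
| 31 | 0.0298 | 0.7307 |
| 32 | 0.0165 | 0.6439 |

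The stated pair is not reproduced. For the printed rule the error ratio is 0.0832 / 0.0487 = 1.71, and the power difference is 0.8661 − 0.8010 = 0.0651.

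**Step 2: could another cut-off give the pair?** The tail falls steadily as r rises. The stated 0.0487 lies between the values at 30 (0.0511) and 31 (0.0298), so no cut-off produces it. The stated power of 0.8010 likewise falls between 0.8055 and 0.7307.

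**Step 3: could another method give it at 29?** The null mean is 66 × 0.35 = 23.1 and the standard deviation is √(66 × 0.35 × 0.65) = 3.875.

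- Score: z = (29 − 23.1) / 3.875 = 1.523, one-sided p = 0.0639
- Score with continuity correction: 0.0817
- Wald: 0.0717
- Arcsine: 0.0684
- Mid-p: 0.0672

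All exceed 0.05. The nearest approximation is at 30 rather than 29: with continuity correction it gives 0.0493 and 0.8056, which is still not the stated pair.

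**Step 4: other explanations.**

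- A 34% null, the reference the article uses for its secondary endpoint, gives an error of 0.0596 at 29 and 0.0352 at 30.
- A search over two-stage futility designs ending at 66 came closest at 0.0497 and 0.8001, with final rejection at 30 or more. The article describes no such design.

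**Step 5: rule against test.**

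| Satisfied of 66 | Printed rule | Score p (one-sided) | Exact p (one-sided) |
|---|---|---|---|
| 29 | rejects | 0.064 | 0.083 |
| 30 | rejects | 0.037 | 0.051 |
| 31 | rejects | 0.021 | 0.030 |

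At 29 neither form of the one-sample test rejects at one-sided 5%, yet the rule does. At 30 the ordinary score test agrees with the rule.

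**Step 6: is 66 itself at fault?** The usual normal-approximation formula, one-sided 5% and 80% power, gives

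n = (1.645 × √(0.35 × 0.65) + 0.842 × 0.5)² / 0.15² ≈ 64.6, that is 65.

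So 66 is a reasonable size on that basis. The fault is in the cut-off and the figures attached to it.

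**The case against.** The strongest reply is about consequence. This is a single-site, single-arm pilot, and the 35% reference is openly a proxy. The estimate and interval will be reported whatever the cut-off. Moving the cut-off from 29 to 31 changes the conclusion only if the count is 29 or 30, which has probability 0.053 at a true rate of 35% and 0.135 at 50%. The printed rule also has more power than claimed, so nobody should infer that the study is underpowered because of it. All of this stands and limits the practical effect. It does not make the stated error rate true.

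A second reply is that the author meant more than 29, that is 30 or more, which lies close to the stated pair. This is plausible but an inference. Its exact error is 0.0511, not 0.0487, and the printed rule would still need changing.

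A reader might also infer that rule, test and interval give opposite answers at both 29 and 30. The document does not support that. It names a one-sample proportion test without calling it exact, and at 30 of 66 the ordinary score test (p = 0.037) agrees with the rule. Nor does the interval contradict the rule. At 29 of 66 the two-sided Clopper-Pearson interval, 31.7% to 56.7%, does contain 35%, but the article gives the interval for estimation and does not make exclusion of 35% a criterion. A two-sided 95% interval beside a one-sided test is expected to differ near the boundary: even at 31 of 66 its lower limit is 34.6%.

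**Conclusion.** The point holds for the decision rule and its stated properties. The printed rule has exact type I error 0.0832 and power 0.8661, against 0.0487 and 0.8010 as stated, and no single-stage cut-off at 66 gives the stated pair. The only clear conflict between rule and test is at exactly 29 of 66.

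This rests on a single-stage design with 66 evaluable responses and independent binomial outcomes, as the section implies. The 5% level used to judge the test at 29 is an assumption taken from the stated 0.0487, since the section names no nominal level. How the mismatch arose cannot be settled from the document. Because this is the primary decision rule, it should be corrected before results are read against it.

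**What to change.** Keep 66 participants and restate the rule, the test and the operating characteristics together.

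- **Preferred:** reject if 31 or more of 66 are satisfied, by the exact binomial test, with one-sided type I error 0.0298 and power 0.7307 at a true rate of 50%. The cost is a stated power below 80%.
- **If 30 or more was intended:** print 0.0511 and 0.8055 as that rule's true error and power, and do not describe it as an exact 5% test. Pairing it with an exact test at 5% would recreate the mismatch, because the exact p at 30 is 0.0511 and the one-sided 95% lower bound is 34.94%, just below 35%.

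The two-sided 95% interval may stay as a descriptive estimate, with a sentence saying that it is not the decision criterion.

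Either option changes one paragraph and needs no further participants. Holding both 5% and 80% exactly is not possible at 66. The smallest design that does so is 31 or more of 68 (0.0461 and 0.8019), which costs two more participants.

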### Electronic medical record review

A secondary objective of this study is to obtain a preliminary estimate of efficacy. In this study, preliminary efficacy will be based on the extent to which the Trial Library intervention promotes discussion of and recruitment to clinical trials. The endpoints of clinical trial discussion documentation will be measured by electronic medical record review. Recruitment to clinical trials will be measured through electronic medical record review approximately 30 days after the participant is enrolled on the Trial Library intervention study.

In the literature, 34% of patients receiving usual care without additional online health information about cancer clinical trials had discussion about clinical trials based on audio recordings of the oncologist consultation [40]. Given that the literature lacks a baseline rate of documentation of clinical trial discussion, 34% will be used as the reference in this study. To evaluate if the Trial Library intervention increases the proportion of participants with documented clinical trial discussion, a one-sample proportion test will be used compared to a reference of 34%.

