### Qualitative semi-structured interview

An exploratory objective of this study is feasibility. Feasibility will be measured through semi-structured interviews and clinical data, such as impact on duration of visit and wait time. As described in Table 2, semi-structured interviews will be performed with a subset of participants (10–12) and all practice physicians seeing eligible patients (6) to assess feasibility and acceptability of the intervention. Interview participants will be identified through convenience sampling. Semi-structured interviews involve use of open-ended questions and probes to elicit descriptive data. Most studies suggest saturation, or retrieval of no new information, is achieved with 8 participants [41]. In this study, telephone interviews will be conducted approximately 7 days after the participant enrolls in the Trial Library study. Physician interviews will occur in-person after clinic visits or within 7 days of encounter with participant. The interviews will use open-ended questions, and participant responses will be recorded, transcribed, and analyzed using thematic analysis. An analysis of saturation will be performed with two researchers coding transcripts of interviews. The researchers will meet to compare and reconcile code, discuss discrepancies, and achieve consensus on each transcript. If saturation is not achieved, up to 8 additional participants may be recruited for interview.

Moreover, data will be extracted from the real-time locating system for hospitals (RTLS), a location technology platform currently instituted as part of standard of care at HDFCCC. RTLS is a system used to provide immediate or real-time tracking and management of staff and patients. This data will be utilized to evaluate the impact that in-clinic use of the Trial Library tool has on the duration of each clinic visit. These measures will be used to assess the feasibility of this intervention. While in the clinic, all patients and doctors wear a locating sensor which is used to gather data on location and visit duration. Investigators will collect participant wait time and length with provider during clinic visit from the RTLS data. The data gathered for participants will be compared to a historical baseline generated by 66 patients who meet the study eligibility criteria but who presented to the clinic prior to the initiation of this study.

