To evaluate if the Trial Library intervention increases clinic length time, a two-sample *t* test will be used to compare minute average of study participants with the reference group (deidentified minute average of new patients seen at HDFCCC prior to initiation of study).

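### The visit-time comparison with historical patients ignores which of six physicians saw each patient; a physician factor is a cheap safeguard, and the documentation rate should be shown by physician

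*Protocol article*

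**What the plan says.** **Patients and physicians.** Under Sample size and justification: "The sample size for this study is 66 participants". Under Qualitative semi-structured interview, the physicians to be interviewed are "all practice physicians seeing eligible patients (6" in brackets, that is, six.

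**Clinic time (exploratory, feasibility).** The same section says: "Investigators will collect participant wait time and length with provider during clinic visit from the RTLS data". The comparator is a "historical baseline generated by 66 patients who meet the study eligibility criteria" and who attended before the study began. A two-sample t test "will be used to compare minute average of study participants with the reference group", which is described there as deidentified. The comparator is defined by eligibility and calendar time. Nothing is said about which physicians saw these patients.

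**Documented discussion (secondary, preliminary efficacy).** Under Methods: "Efficacy will be determined by whether a clinical trial discussion was documented in the electronic medical record during the clinic visit". Under Electronic medical record review, the rate is set against an outside figure: "a one-sample proportion test will be used compared to a reference of 34"%.

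No significance level is stated for either test, and no interval is planned for either outcome. The only interval in the article is for satisfaction.

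**The concern.** How long a visit lasts, and whether a trial discussion reaches the chart, plausibly depend on the physician. That is an inference; the article does not say so. Both named tests treat the 66 participants as independent.

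For clinic time, the question is whether the tool lengthens visits. If a slower physician saw more patients in one period than in the other, that difference is added to or subtracted from the apparent effect of the tool. If the mix is the same, physician differences cancel from the comparison but stay in the t test's error term, which costs some precision.

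For documentation the reference is a fixed outside number, so nothing cancels. If physicians are viewed as a sample, the ordinary binomial standard error is too small. The study is meant to supply preliminary data for a multi-site randomised trial, so an over-precise rate could mislead its planning.

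**Working it through.** The plan gives no error rate, power or intraclass correlation (ICC) for either test, so there is no stated figure to reproduce. Inputs from the article: 66 participants, 66 historical patients, 6 physicians, reference 34%. Assumed: the ICC, shown over a range, and the split of patients by physician.

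**1. Clinic time, same mix in both periods (11 per physician).** Set the total variance to 1. Physician effects cancel, so the true variance of the difference is (1 − ICC) × 2/66. The t test estimates it as [(1 − ICC) + ICC × (5/6) × 66/65] × 2/66. At ICC 0.10 these are 0.0273 and 0.0298. The true standard error is √(0.0273/0.0298) = 0.956 of the one used, so the test is conservative. Simulated two-sided error at nominal 0.05 (nominal level assumed): 0.045 / 0.040 / 0.034 at ICC 0.05 / 0.10 / 0.20.

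**2. Clinic time, strongly different mix.** Assumed splits are 24, 16, 10, 8, 5, 3 in one period and 5, 8, 10, 3, 24, 16 in the other.
- Differences in count: 19, 8, 0, 5, −19, −13. Their squares sum to 980, and 980/66² = 0.225.
- True variance of the difference: ICC × 0.225 + (1 − ICC) × 2/66. At ICC 0.10 this is 0.0225 + 0.0273 = 0.0498.
- Within each period the squared shares sum to 1030/66² = 0.236. The t test uses [(1 − ICC) + ICC × (1 − 0.236) × 66/65] × 2/66 = 0.0296.
- The true standard error is √(0.0498/0.0296) = 1.30 times the one used. The error is 2 × [1 − Φ(1.96/1.30)] ≈ 0.13.

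| ICC | Simulated error, same mix | Simulated error, strongly different mix |
|---|---|---|
| 0.05 | 0.045 | 0.087 |
| 0.10 | 0.040 | 0.132 |
| 0.20 | 0.034 | 0.203 |

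**3. Same model with physician as a fixed factor.** If physician effects are stable over time they drop out. Simulated error stays near 0.05 under both mixes. Residual degrees of freedom fall from 130 to 125. With the different mix, the variance of the period effect is (1 − ICC)/Σ[n₁n₂/(n₁ + n₂)], and the sum is 4.14 + 5.33 + 5.00 + 2.18 + 4.14 + 2.53 = 23.3, against 33 with equal splits. At ICC 0.10 this gives 0.9/23.3 = 0.0386, below the unadjusted true variance of 0.0498 but above the 0.0296 that the t test would report. So the adjusted interval is honestly wider there.

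**4. Limit of the adjustment.** If half of the physician variance is not stable across periods, the unadjusted t test has error 0.078 / 0.110 / 0.159 even with the same mix. A fixed physician factor does not remove that.

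**5. Documentation against 34%, 6 × 11 patients.** Design effect = 1 + (11 − 1) × ICC.

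| ICC | Design effect | Standard error ratio | 95% half-width at 34% |
|---|---|---|---|
| 0 | 1.0 | 1.00 | 11.4 points |
| 0.02 | 1.2 | 1.10 | 12.5 points |
| 0.05 | 1.5 | 1.22 | 14.0 points |
| 0.10 | 2.0 | 1.41 | 16.2 points |

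For illustration, a cut-off of 30 or more of 66 (not in the plan) has exact error 0.035 under independence and simulated error of about 0.05 / 0.07 / 0.10 at ICC 0.02 / 0.05 / 0.10.

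**6. Documentation, six physicians taken as fixed.** With assumed rates of 10, 20, 30, 40, 50 and 54% (mean 34%), a cut-off of 29 or more has error 0.049, against 0.060 if every patient has the same 34% rate. There is no inflation on this reading.

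**The case against.** A reader might infer that both tests have error above nominal and intervals that are too narrow. The documents do not support that. No ICC is given, no significance level is stated for either test, and no interval is planned for either outcome. For clinic time the comparator comes from the same clinic, and if the same physicians saw both groups in a similar mix the t test is conservative. Nothing in the article says that the mix changed. For documentation, all six physicians of the practice are included, and inference limited to them shows no inflation. All of this stands.

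The fixed-physician argument has a limit. The 34% comes from audio-recorded consultations elsewhere, and nothing makes these six physicians' own average equal 34% when the tool has no effect.

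It may also be said that adjustment factors belong in an analysis plan that is not shown. That is fair in general, and it lowers the weight of the point. But the article does name the t test, and whether the deidentified historical extract keeps a physician code must be settled before the data are pulled.

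A tempting stronger remedy is to compare documentation before and during the study within physician. The historical patients are described only for the time comparison, so this would need chart review that is not planned. It is not a change of wording and is not asked for here.

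**Conclusion.** The point holds in a limited form. The clinic-time comparison is open to confounding by physician if the mix differs between periods (error 0.087 to 0.203 at ICC 0.05 to 0.20 under the assumed, deliberately strong shift). It is mildly conservative if the mix is the same. Either way a physician factor is the better analysis, provided physician effects are reasonably stable over time. For documentation, the ordinary standard error would need to be about 10% to 41% larger at assumed ICC 0.02 to 0.10 if the physicians are taken as a sample, and no larger if inference stops at these six. The actual sizes cannot be known from the documents. The outcomes are secondary and exploratory in a pilot, and the primary satisfaction analysis is outside this point, so this is a low-cost improvement and not a threat to the study's main conclusion.

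**What to change.** **Clinic time.** Replace the two-sample t test with a linear model of visit time, and likewise of time with provider, on period (study or historical) with physician as a fixed factor. Report the period difference with its interval, and tabulate patients by physician in each period. Keep a physician code, without names, in the deidentified locating-system extract for both groups. Physicians as well as patients wear sensors, so the system should be able to supply it.

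**Documentation.** Report the rate by physician beside the overall rate. Then either state that inference is limited to these six physicians, or add an interval that allows for clustering with a small-sample correction, for example one based on the six physician rates and a t distribution with five degrees of freedom.

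**Cost.** Five degrees of freedom in the time model, a wider but honest interval if the mix differs, and confirmation that the historical extract can carry the code. If it cannot, keep the unadjusted comparison and state that it is not adjusted for physician. The documentation change is wording and one table; an interval resting on six clusters will be wide.
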